##### Attitude

Attitude towards self-testing for diabetes or cholesterol will be measured using a four item scale developed by Marteau [26]. Participants are asked to respond to the following questions on a 7-point Likert scale: I think self-testing is: harmful--beneficial; unimportant--important; bad thing--good thing; unpleasant--pleasant. Responses are used to classify people as having a positive or a negative attitude. Scores range from 4 to 28, with higher scores referring to a more positive attitude towards self-testing. Whether the participant has a positive or negative attitude towards self-testing will be determined using the median of the scores of the participants [26].

##### Ambivalence

Felt ambivalence will be assessed using a 3 item scale as described by Priester and Petty [24].

##### Psychosocial determinants

Possible determinants of self-test use were derived from the Health Belief Model (HBM) [16], as well as several concepts of the Theory of Planned Behavior (TPB) [17] and will be assessed after participants have viewed the decision aid or control condition.

##### Behaviour

Behaviour will be measured 3 months after the intervention. Participants will be asked whether they have performed a self-test for cholesterol or diabetes, and whether they have visited a doctor or have changed their lifestyle in the past 3 months, in response to having viewed the decision aid. If they have performed a self-test, they will be asked what the result of the self-test was (normal test result, abnormal test result) and the actions taken based on this test result.

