### Study aim and research questions

The principal aim of the proposed study is to evaluate the effect of the decision aid on knowledge of on self-testing. The following research questions were formulated:

1. Do consumers who have been exposed to the decision aid have more knowledge of self-testing than the control group?

2. Do consumers who have been exposed to the decision aid more often make an informed choice in self-testing than consumers in the control group?

3. Do the intervention and control groups differ in level of attitudinal ambivalence?

4. What is the effect of the decision aid on the psychosocial factors that predict self-test use for diabetes and cholesterol?

5. Is there a difference between the intervention and control group in follow-up behaviour 3 months after the use of the decision aid?

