### Control condition

A placebo control condition was designed consisting of general information on self-testing. An existing control condition was not available, since there is no usual care in self-testing. Our intervention is the first decision aid that aims at people with an intention towards self-testing, and, to the best of our knowledge, is the first non-commercial website that provides test specific information on cholesterol and diabetes self-testing. The control condition will consist of a pdf file of one page which gives general information on self-testing (definition of a self-test and the types of self-tests that are available). It does not include test specific information or interactive elements that are included in the original decision aid since these are distinguishing features of our decision aid.

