### Methods of data collection

An overview of all questionnaires and measures is provided in Table 2 and Figure 1.

**Table 2 T2:** Outcome measures and timing of data collection

Construct	Measures	No. of items	Questionnaire*
*Primary outcomes*			
Knowledge	Knowledge questionnaire based on information provided in the decision aid	20 Statements (True/false/don't know)	2
*Secondary outcomes*			
Attitude	Marteau [26]	4	1,2
Ambivalence	Felt ambivalence [24]	3	1,2
Follow-up behaviour	Uptake of self-tests, visiting a doctor, changing lifestyle.	7	3
Intention	Intention towards self-testing, seeing a doctor.	2	1,2,3
	Intention towards changing lifestyle	1	2,3
	Stages of change [27]	1	1,2,3
Psychosocial determinants	Perceived benefits and barriers	14	2
	Self-efficacy	3	2
	Response-efficacy	4	2
	Perceived susceptibility/risk perception [28]	3	1,2,3
	Cues to action	1	2
	Perceived severity	1	2
	Anticipated regret	1	2
	Moral obligation	2	2
	Subjective norm	1	2

*Questionnaire 1: baseline. Questionnaire 2: directly after seeing intervention or control condition. Questionnaire 3: three months after viewing intervention or control condition

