**Figure 1 F1:**
[figure not shown]
**Selection of participants and randomization**.

Questionnaire 1 will be sent to a random sample of the Flycatcher panel and is aimed at selecting consumers with an intention towards self-testing for diabetes or cholesterol. The questionnaire will consist of questions on personal characteristics (including medical history of cardiovascular disease and diabetes, and risk factors), and intention towards doing a cholesterol or diabetes self-test. (Additional file 1). A translation of the questionnaires (originally in Dutch) is provided in the additional data files.

Questionnaire 2 will be sent after participants have been assigned to the intervention or control condition and have been exposed to this condition. Participants with an intention to do a cholesterol self-test will receive questions on cholesterol self-testing (Additional file 2), participants with an intention to do a diabetes self-test will receive a similar questionnaire, but addressing the diabetes self-test (Additional file 3).

Three months after participants have viewed the decision aid or the control condition, they will be sent questionnaire 3 (Additional file 4), which includes questions on self-test use in the past 3 months, intention towards doing a self-test, visiting a doctor or changing lifestyle.

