### Statistical analysis

Knowledge will be treated as primary outcome measure, whereas intention, attitude, ambivalence and psychosocial variables are the secondary outcome measures. To compare knowledge levels and level of ambivalence between the intervention and control group, we will use linear regression analysis. The effect of the decision aid on the psychosocial factors that predict self-test use will be assessed using logistic regression analysis. Follow-up behaviour after 3 months will be compared using logistic regression analysis.

Based on the method proposed by Marteau and colleagues, informed choice will be measured by combining the constructs knowledge, attitudes and behaviour into a composite measure of informed decision making [26]. Informed choice in our study will be defined as having sufficient knowledge, and attitude being in line with intention (positive attitude and a positive intention to do a self-test, or a negative attitude and a negative intention to self-test). As a cut off point for having sufficient knowledge, a score of 50% (number of correct answered questions 10 or above) will be considered. Individual scores will be corrected for guessing using Abbotts' formula [31,32]. A positive intention towards self-testing is defined as a participant indicating to maybe, probably or definitely consider performing a self-test in the future. To classify participants as having a positive or negative attitude towards self-testing, the median score will be used. The median score of the participants and scores above will indicate a positive attitude, whereas scores below the median score will be considered as a negative attitude [26]. The percentage of people with an informed choice in the control and intervention group will be compared using logistic regression analysis.

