## Discussion

This paper describes the protocol for a randomised controlled trial to evaluate the effect of an online decision aid for self-testing on diabetes and cholesterol. Since self-testing on these conditions can be beneficial but can have negative implications as well, the goal of the decision aid 'zelftestwijzer' was not to increase or decrease uptake of these tests, but to enhance knowledge levels and to guide the decision making process. Self-testing uptake in the past often seemed to be associated with offering of free tests and media campaigns stressing the importance of testing, and consumers responding quite straightforward, being curious about testing and wanting to be reassured on their health status [9]. Although these strategies seemed to increase uptake levels, consumers will often not have considered important pitfalls of self-testing [3]. Also, consumers with an intention towards self-testing experience several barriers to self-testing, especially a lack of knowledge on interpreting the results ([name] et al: An intention to self-testing: a qualitative study regarding consumers' considerations and information needs about self-testing, submitted). For this reason, the primary outcome of this study is knowledge of on self-testing. We expect knowledge levels of participants who have viewed the decision aid to increase. Being aware of the pitfalls of self-testing, but also of the positive effects of self-testing, consumers should be enabled to make a choice regarding self-testing they think is the best choice for them. We expect levels of informed choice to increase, and levels of ambivalence to decrease. We will measure actual uptake of self-tests 3 months after viewing the decision aid, to assess if there are changes in uptake of tests between the intervention and the control group.

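### The Behaviour section ties doctor visits and lifestyle change to viewing the decision aid, which controls never see, yet these answers are compared between arms

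*Protocol article*

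**What the plan says.** Research question 5 in the protocol article is a between-arm question: "Is there a difference between the intervention and control group in follow-up behaviour 3 months after the use of the decision aid". The Statistical analysis section answers it with a model: "Follow-up behaviour after 3 months will be compared using logistic regression analysis".

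The outcome is described in four places.

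- **Behaviour section.** Participants are asked whether they have done a self-test, and whether they "have visited a doctor or have changed their lifestyle in the past 3 months, in response to having viewed the decision aid". No separate version for controls is described.
- **Table 2.** Follow-up behaviour has seven items in questionnaire 3: "Uptake of self-tests, visiting a doctor, changing lifestyle". There is no attribution clause.
- **Methods of data collection, text below Figure 1.** "Three months after participants have viewed the decision aid or the control condition, they will be sent questionnaire 3", "which includes questions on self-test use in the past 3 months, intention towards doing a self-test, visiting a doctor or changing lifestyle". The items themselves are in Additional file 4, which is not shown.
- **Discussion.** Actual uptake is measured "to assess if there are changes in uptake of tests between the intervention and the control group", again without attribution.

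On exposure, the Control condition section says: "The control condition will consist of a pdf file of one page which gives general information on self-testing". That page defines a self-test and lists the types available. Under Strengths and limitations the article adds that controls had already been given this information in the baseline questionnaire. The decision aid, by contrast, includes advice on when to see a doctor and material on lifestyle change (Table 1).

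**The concern.** A between-arm comparison needs the outcome to be recorded in the same way in both arms. As the Behaviour section words it, a visit or a change counts only if the participant puts it down to viewing the decision aid. A control participant who saw a doctor during the three months would, on a literal reading, have to answer no. The logistic regression would then compare behaviour credited to the aid with a question that controls can hardly answer yes to.

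Randomisation already supplies the causal attribution. Asking participants to supply it again adds nothing to the comparison except reporting that depends on the arm. At stake is the answer to research question 5 for two of its three components. An apparent effect on doctor visits and lifestyle change could arise when true behaviour is the same in both arms.

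**Working it through.** **1. Setting the descriptions side by side.** The clause clearly attaches to the doctor visit and the lifestyle change. Whether it also reaches back to self-test uptake is grammatically open, but uptake is described without it in Table 2, under Methods of data collection and in the Discussion. For doctor visits and lifestyle change, Table 2 is the clear neutral description. The sentence under Methods of data collection could be listing them as behaviours or as intentions.

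**2. Would a parallel clause for controls help?** Suppose controls were asked about acting in response to the information they had received. The control page contains no advice on doctors or lifestyle and repeats text seen at baseline, whereas the aid contains both kinds of advice. The arms would still be attributing to unlike stimuli, and controls would have little to attribute a visit to. A parallel clause does not make the answers comparable.

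**3. Figures in the article.** None concerns behaviour. The group size used below, 175 in each of four groups, is planned for knowledge (70% against 55%, 5% two-sided, 80% power). The two-proportion formula gives 163 per group without and 176 with continuity correction, so 175 is reproduced closely. The invitation figure also reproduces: 4 × 175 / (0.60 × 0.80 × 0.42) = 3472.

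**4. Illustration under assumed rates.** Let the true rate r be equal in both arms, so there is no effect. The intervention arm reports a fraction f1 of its behaviour and controls a fraction f0. Then p1 = r·f1, p0 = r·f0, the spurious difference is p1 − p0, and with p̄ the mean of p1 and p0,

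P(significant) = Φ{ [(p1 − p0) − 1.96·√(2p̄(1 − p̄)/n)] / √[(p1(1 − p1) + p0(1 − p0))/n] }.

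With r = 20%, f1 = 1 and f0 = 0.5: p1 = 0.20, p0 = 0.10, p̄ = 0.15. The odds ratio is (0.20/0.80)/(0.10/0.90) = 2.25.

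- n = 175: (0.10 − 1.96 × 0.0382)/0.0378 = 0.67, and Φ(0.67) is about 0.75.
- n = 350 (diabetes and cholesterol groups pooled): (0.10 − 1.96 × 0.0270)/0.0267 = 1.76, and Φ(1.76) is about 0.96.

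| True rate, both arms | Reported fraction, intervention / control | Spurious difference (points) | P(significant), n = 175 | P(significant), n = 350 |
|---|---|---|---|---|
| 5% | 1 / 0.5 | 2.5 | 0.23 | 0.41 |
| 10% | 1 / 0.5 | 5 | 0.43 | 0.71 |
| 20% | 1 / 0.5 | 10 | 0.75 | 0.96 |
| 30% | 1 / 0.5 | 15 | 0.92 | 0.998 |
| 20% | 0.5 / 0.25 | 5 | 0.43 | 0.71 |
| any | equal (neutral items) | 0 | 0.05 | 0.05 |

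The fifth row lets the clause lower reporting in the intervention arm as well. If controls cannot answer yes at all and the intervention arm reports everything, the spurious difference equals the true rate. Any dropout before month 3 would lower these probabilities but would not shrink the spurious difference.

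**The case against.** The strongest reply is that the Behaviour section summarises the questionnaire and does not reproduce it. The items are in Additional file 4, and they may be neutral or may exist in a control version. The article also uses the decision aid loosely as a name for the exposure in both arms: research question 5 dates follow-up from use of the aid for intervention and control alike, and the Discussion does the same for uptake. The clause may be the same shorthand. This stands as a reason for caution, so the bias is a conditional risk and has not been shown. It does not remove the inconsistency, because the section just before, on psychosocial determinants, names both conditions where both are meant.

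It is also fair to say that an attribution clause would lower reporting in the intervention arm, since unrelated visits would not count. Assuming full reporting there therefore enlarges the gap. This stands too, and is why the table carries a row with reduced reporting in both arms.

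A reader might infer that the item also breaks the blinding, which the article claims as a strength, by telling controls about an aid they were not shown. That would follow only if controls received the literal wording, and no part of the article says they will. Questionnaire 3 also comes after knowledge has been measured, so the primary outcome would not be touched.

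**Conclusion.** The point holds in conditional form, with moderate confidence. The article defines two of the three follow-up behaviours by attribution to something controls never see, describes the outcome elsewhere without that condition, and compares it between arms. If the questionnaire follows the Behaviour section, the arms are not measured alike and the bias runs towards more behaviour in the intervention arm.

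The size depends on assumptions, because the article states no behaviour rates. With controls reporting half of their behaviour, the intervention arm reporting all of it, and true rates of 5% to 30%, the chance of a false positive is 23% to 92% at 175 per arm and 41% to 99.8% at 350. With neutral items it is the nominal 5%.

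A reader might go further and infer that the whole 3-month comparison is biased as a matter of fact. The documents do not support that: the item wording is not shown, and self-test uptake is described neutrally in three places. Follow-up behaviour is a secondary outcome, and the primary analysis and sample size do not depend on it. The matter should be corrected but ranks below a must-fix.

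**What to change.** Bring the Behaviour section into line with Table 2, Methods of data collection and the Discussion. State that both arms receive identical, unattributed questions on self-test use, doctor visits and lifestyle change over the preceding three months, and that these answers are the outcomes in the logistic regression. If participants' own attribution is of interest, ask it after those items and report it descriptively with the process evaluation.

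First check Additional file 4. If its items are already neutral, one sentence in the Behaviour section needs changing. If they carry the clause, a few items need rewording before questionnaire 3 is sent. Neither case changes the design, sample size or analysis model. Once attributed answers have been collected, unattributed behaviour cannot be recovered from them. In that event, doctor visits and lifestyle change should be reported as self-attributed responses and not as a randomised comparison of behaviour.

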### Process evaluation

Message acceptance will be measured on an eight item scale, for example, 'The information provided on the website is very realistic/realistic/neutral/not realistic/not realistic at all' [29]. Participants will be asked to comment on the strong and weak features of the decision aid. Weblog files of each participant will be collected to assess use of the website, time spent on the website and use of each page of the website.

### Sample size

According to a Cochrane review by O'Connor et al. on the efficacy of decision aids, there is an average absolute increase of 15% in knowledge scores when decision aids are compared to usual care. When more detailed decision aids are compared to simpler decision aids, knowledge increases with 5% [11]. Since we will compare our decision aid to general, non test specific information on self-testing, we expect an increase in knowledge of 15% (intervention group knowledge score 70%, control group 55%). Our sample size will be based on a power of 80% to detect a hypothesized increase in knowledge of 15% at a significance level of 5% (two-sided). Power analysis showed 175 respondents would be needed in each of the four groups [30]. Based on previous research, a completion rate of 60% on the first questionnaire, and 80% on the second questionnaire is expected [3]. Intention towards doing a cholesterol and/or a diabetes self-test in 2008 was 42%. Based on these results, a minimum of 3472 respondents would have to be invited for the first questionnaire. Since we do not know intention rate in 2011, and an unknown number of participants will be excluded because of having cardiovascular disease or diabetes, we decided to invite 6000 panel members for the first questionnaire.

### Statistical analysis

Knowledge will be treated as primary outcome measure, whereas intention, attitude, ambivalence and psychosocial variables are the secondary outcome measures. To compare knowledge levels and level of ambivalence between the intervention and control group, we will use linear regression analysis. The effect of the decision aid on the psychosocial factors that predict self-test use will be assessed using logistic regression analysis. Follow-up behaviour after 3 months will be compared using logistic regression analysis.

Based on the method proposed by Marteau and colleagues, informed choice will be measured by combining the constructs knowledge, attitudes and behaviour into a composite measure of informed decision making [26]. Informed choice in our study will be defined as having sufficient knowledge, and attitude being in line with intention (positive attitude and a positive intention to do a self-test, or a negative attitude and a negative intention to self-test). As a cut off point for having sufficient knowledge, a score of 50% (number of correct answered questions 10 or above) will be considered. Individual scores will be corrected for guessing using Abbotts' formula [31,32]. A positive intention towards self-testing is defined as a participant indicating to maybe, probably or definitely consider performing a self-test in the future. To classify participants as having a positive or negative attitude towards self-testing, the median score will be used. The median score of the participants and scores above will indicate a positive attitude, whereas scores below the median score will be considered as a negative attitude [26]. The percentage of people with an informed choice in the control and intervention group will be compared using logistic regression analysis.

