### Randomisation

Participants will be assigned to one of two groups (having an intention towards doing a cholesterol or towards doing a diabetes self-test). If participants have an intention to do both, they will be assigned to the test towards which they have the strongest intention. Within each group, randomisation over experimental conditions (and invitation to view either the decision aid or the control condition) will be performed by Flycatcher using SPSS. Participants will be blinded for randomisation.

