### Measures

#### Primary outcome

##### Knowledge

Knowledge questions are based on the themes that are addressed in the decision aid. It includes questions on the condition, indications for testing, such as symptoms and risk factors, what the test measures, how to interpret the test result, and questions on the validity of the self-test. These aspects of self-testing were deemed important by health professionals as well as indicated by end-users [9]([name] et al: Quality and use of consumer information provided with home test kits: Room for improvement, submitted). This knowledge quiz consists of 20 true/false statements. Knowledge questions are test specific, and differ between the cholesterol and diabetes self-test.

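### The size is set for two test-specific comparisons, but the stated primary analysis is one intervention-versus-control regression that does not mention test group

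*Protocol article*

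**What the plan says.** Four statements in the protocol article bear on this.

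- **Randomisation.** Participants are first placed in a cholesterol or a diabetes group, according to the test they intend to use. Allocation to decision aid or control is then made inside that group: "Within each group, randomisation over experimental conditions". Test group is thus a randomisation stratum.
- **Knowledge (primary outcome).** The quiz has 20 statements, and the two groups do not answer the same one: "Knowledge questions are test specific, and differ between the cholesterol and diabetes self-test".
- **Sample size.** The hypothesised knowledge scores are 70% and 55%, with 80% power and a two-sided 5% level. The result is that "175 respondents would be needed in each of the four groups".
- **Statistical analysis.** "To compare knowledge levels and level of ambivalence between the intervention and control group, we will use linear regression analysis". Informed choice and three-month behaviour are compared by logistic regression, also without mention of test group. The section names no stratum term, interaction or separate analysis by test.

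The research questions are likewise worded as one contrast between those who saw the decision aid and the control group.

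**The concern.** The design treats cholesterol and diabetes as two parallel trials: separate randomisation, separate quizzes, and a full two-arm sample for each. The analysis section reads as one trial with one contrast. The number of primary tests and the quantity being estimated depend on which section is followed.

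If the analysis section is followed as written, scores from two different instruments go on one scale and the stratum used for allocation is left out. Any gap in difficulty between the quizzes becomes unexplained variation, and a difference in effect between the tests goes unexamined. If the sample-size section is followed, there are two primary comparisons, and the article does not say whether each answers its own question at 5% or whether success on either one counts.

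**Working it through.** **Inputs.** From the Sample size section: 55% against 70%, power 80%, two-sided 5%, 175 per group, four groups, completion rates 60% and 80%, intention rate 42%. Assumed: 1:1 allocation and equal-sized test groups (the four groups are given the same size), and the gap in quiz difficulty (the article gives neither an SD nor a gap).

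**1. What 175 is.** Two-proportion formula with mean proportion 0.625:

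n = [1.960 × √(2 × 0.625 × 0.375) + 0.842 × √(0.55 × 0.45 + 0.70 × 0.30)]² / 0.15² = (1.342 + 0.569)² / 0.0225 ≈ 162.3, so 163 per arm.

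With continuity correction: (162.3 / 4) × [1 + √(1 + 4 / (162.3 × 0.15))]² ≈ 175.4, so 176 rounded up. The protocol's 175 is therefore the per-arm size for **one** two-arm comparison.

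**2. What the total is.** 4 × 175 = 700 completers. Invitations: 700 / 0.80 / 0.42 / 0.60 = 3472, the protocol's own minimum. The trial is sized at two such comparisons, one per test.

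**3. Power on the same inputs, without continuity correction.**

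| Comparison | Per arm | Calculation | Power |
|---|---|---|---|
| One test group | 175 | (0.15 − 1.960 × 0.0518) / 0.0511 = 0.95 | 82.9% |
| Both groups together | 350 | (0.15 − 1.960 × 0.0366) / 0.0362 = 2.17 | 98.5% |

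A single overall comparison would reach the planned 80% with about 176 per arm, or 352 people. A total of 700 fits two comparisons.

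**4. Cost of leaving the stratum out.** If the quizzes differ in mean by d within-group SDs and the test groups are equal in size, the omitted term adds d²/4 to the residual variance, in units of the within-group variance. The model standard error is then multiplied by √(1 + d²/4):

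- d = 0.5: √1.0625 = 1.031, about 3%.
- d = 1: √1.25 = 1.118, about 12%.

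Unequal test groups give less, because the added variance is p(1 − p)d², where p is the share of participants in one test group; this is largest at p = 0.5.

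**5. Two primary tests at 5% each.** The samples are disjoint, so the chance of at least one false positive when both nulls are true is 1 − 0.95² = 9.75%.

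**The case against.** The strongest reply is that pooling is inferred from singular wording. The analysis section gives no covariate list for any model, and a test-group term could be present but unstated. A journal article condenses, and covariates are often left to an analysis plan that is not shown here. Read with the other sections, the comparison could also be meant within each test group. A trial may also be sized per stratum and still have one overall primary test.

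Much of this stands. A reader might infer that the investigators have decided to ignore test group, or that the choice will be made after the data are seen. The article supports neither: it is silent on test group in the models, and an analysis plan may settle the matter.

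A reader might also infer that the arm comparison is biased. It is not if allocation is balanced within test groups. The inflated model standard error makes the test conservative, and the loss in power would be small: on the 70% and 55% inputs, even 12% inflation leaves roughly 96% (4.15 / 1.118 = 3.71; 3.71 − 1.96 = 1.75).

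Nor can 9.75% be given as the trial's error rate. It needs both nulls to be true and a claim of success on either test, and the article states no such rule. Two distinct questions in separate participants can reasonably each be tested at 5%.

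What the reply does not remove is the mismatch. The article states both its sizing and its primary model, and the first is built for two comparisons while the second describes one. That goes beyond detail deferred to another document.

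**Conclusion.** The point holds as a mismatch between the sizing and the stated primary analysis, together with the absence of the randomisation stratum from that analysis as written. The sizing part rests on the protocol's own figures: 175 reproduces (175.4 before rounding up) as one two-arm comparison, and 3472 reproduces from four groups of 175.

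The precision cost is modest and conditional. It is 3% to 12% on the standard error for assumed difficulty gaps of 0.5 to 1 SD with equal test groups, and nothing if the quizzes are equally hard. No bias in the arm contrast is shown. A familywise error of up to 9.75% arises only under an either-test claim. The correction is worth making because it concerns the primary outcome and costs almost nothing; it does not threaten the trial.

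**What to change.** **Preferred.** Make the single primary analysis a linear regression of knowledge score on arm and test group, at two-sided 5%. Carry the test-group term into the other regression models. Report the arm-by-test-group interaction and the two test-specific estimates as secondary. In the sample-size text, say that 175 per cell supports the test-specific estimates and that the overall comparison has about 350 per arm. The cost is one covariate and a few sentences, with no extra participants.

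Two limits should be acknowledged. The adjusted model still averages one effect over two different quizzes, which is why the test-specific estimates should be shown beside it. The interaction can only be estimated coarsely: with 175 per cell and an assumed SD of 15 to 25 points, the smallest difference in effect detectable with 80% power is 2.80 × SD × √(4/175), about 6 to 11 points.

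**Alternative.** If two test-specific primary comparisons are intended, as the sizing suggests, the analysis section and research questions should say so. They should also state whether each is a separate question tested at 5% or whether success on either counts. In the second case an alpha rule is needed. With 2.5% per test, the same continuity-corrected formula gives 210 per arm, so 840 completers and 840 / 0.80 / 0.42 / 0.60 = 4167 invitations. That is within the 6000 planned, before exclusions for existing disease and if the two test groups fill evenly.
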